#### Safety monitoring

Routine blood and urine analyses, electrocardiography, and liver and kidney function tests will be performed before and after treatment. Adverse events and severe adverse events will be recorded at each visit.

### Participant timeline {13}

Recruitment has commenced in April 2019 and will end in April 2022 (Fig. 1). The schedule for registration, intervention, and evaluation are listed in Table 4.

**Fig. 1 Fig1:**
[figure not shown]
Flow diagram of the study process

**Table 4 Tab4:** Schedule of enrollment and assessments

Study period					
Time point	Enrolment	Allocation	Post-allocation		Follow-up
	−1 week	Week 0	Week 4	Week 12	Week 24
Enrolment					
Eligibility screen	×				
Informed consent	×				
Allocation		×			
Interventions					
Zhigancao Tang granules					
Zhigancao Tang granule placebo					
Outcome assessments					
Cardiac function		×	×	×	×
Echocardiography		×	×	×	×
Lee’s scale		×	×	×	×
MLHFQ		×	×	×	×
6MWT		×	×	×	×
NT-pro BNP, ANP		×	×	×	
ITSS		×	×	×	×
Safety assessments					
Blood routine		×		×	
Urine routine		×		×	
Liver and kidney function		×		×	
electrocardiograph		×		×	
AE		×	×	×	×
Compliance assessments			×	×	

AE, adverse events; ANP, atrial natriuretic peptide; ITSS, integral Chinese medicine syndrome score; MLHFQ, Minnesota Living with Heart Failure questionnaire scale; NT-proBNP, N-terminal pro-brain natriuretic peptides

### Sample size {14}

The sample size for this study was calculated based on the expected value of efficacy, according to the clinical trial results and analysis of data from previously published articles [13]. The total efficacy rates in the study and control groups were 93.3% and 73.3%, respectively. The significance level (alpha) was set at 0.05, and the statistical power was set at 80%. Based on our calculation, using the PASW statistical software (V.18.0), the experimental and control groups will each require a sample size of 51 patients. Considering a 20% loss to follow-up, 61 participants are required in each group. Therefore, this trial will require at least 122 participants in the current study.

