## Statistical methods

### Statistical methods for primary and secondary outcomes {20a}

Data analysis will be completed using the Statistical Packages of Social Sciences software (version 24.0). Qualitative indicators will be described in terms of frequency tables, percentages, or component ratios, whereas quantitative measures will be described in terms of mean, median, lower quartile (Q1), upper quartile (Q3), minimum, and maximum. For the comparative analysis of the two groups, the chi-square test, Fisher’s exact probability method, and Wilcoxon rank and inspection will be applied for qualitative data and *t* test will be applied for quantitative data, while the *t* test will be applied for quantitative data with normal distribution. Homogeneity test of variance will be conducted among the groups, with a cutoff level of 0.05, and the Satterthwaite method will be used to conduct the corrected *t* test when the variance is uneven. If the data do not follow normal distribution, the Wilcoxon rank test and inspection will be performed. The two-sided test will be uniformly used in the hypothesis test, and the test statistics and their corresponding *P* values will be provided, with *P* values ≤ 0.05 considered statistically significant and *P* values ≤ 0.01 considered highly statistically significant.

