#### Missing data

Any missing data will be treated as a failure using the intention-to-treat principle, and the reason will be recorded.

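### The sample-size allowance is miscalculated: 61 per group leaves about 49 after 20% loss, not the required 51, and it is not tied to either of two conflicting missing-data rules

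*Protocol article*

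**What the plan says.** All figures are in the protocol article, Sample size {14}. The planning rates are given as "The total efficacy rates in the study and control groups were 93.3% and 73.3%, respectively", with alpha 0.05 and 80% power. From these, "the experimental and control groups will each require a sample size of 51 patients". The allowance for loss follows: "Considering a 20% loss to follow-up, 61 participants are required in each group". The section concludes that "this trial will require at least 122 participants in the current study". Statistical methods {20a} makes the tests two-sided and names the chi-square test first among those for qualitative data.

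Missing outcomes are handled in two places. Under Missing data: "Any missing data will be treated as a failure using the intention-to-treat principle". Section {20c} plans both intention-to-treat and per-protocol analyses, asks researchers to try to obtain a last assessment from patients who drop out, and says that missing data will be filled in by multiple imputation with chained equations. Nothing says which rule governs the primary analysis.

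**The concern.** There are two separate issues, of different certainty.

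The first is arithmetic. To keep a required number after a proportion d is lost, that number is divided by (1 − d). The stated 61 matches multiplication by 1.2 instead, which always gives too few. The minimum of 122 therefore does not do what the section says it does.

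The second is a mismatch between design and analysis. Inflating for dropout makes sense if patients without an outcome leave the denominator and the others respond at 93.3% and 73.3%. If missing outcomes count as failures, those patients stay in, both response rates fall and the difference shrinks. A sample size inflated in the usual way then no longer gives the planned power. Whether this happens depends on which missing-data rule is primary, and the protocol leaves that open. At stake is how a null result is read: it could be taken as coming from a trial with 80% power when the power was lower.

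**Working it through.** **Inputs.** From Sample size {14}: p1 = 0.933, p2 = 0.733, alpha 0.05, power 80%, 51 per group, 20% loss, 61 per group. From {20a}: two-sided testing.

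**1. Reproducing 51.** Normal approximation with unpooled variance:

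n = (1.960 + 0.842)² × [p1(1 − p1) + p2(1 − p2)] / (p1 − p2)²
= 7.849 × (0.0625 + 0.1957) / 0.04 = 50.7, so 51.

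The stated figure reproduces. Exact power of the uncorrected chi-square test at 51 per group is 80.0%.

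**2. The allowance for loss.**

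- 51 × 1.2 = 61.2, which gives the stated 61 when rounded down.
- 61 × 0.8 = 48.8, below 51.
- 51 / 0.8 = 63.75, so 64 per group and 128 in total.
- 1 − 51/61 = 0.164, so 61 per group covers 16.4% loss.

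**3. Cost of that slip alone.** Here dropouts leave the analysis and the rates are unchanged.

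| Completers per group | Power, formula that gives 51 | Power, exact chi-square |
|---|---|---|
| 48 | 77.8% | 79.3% |
| 49 | 78.7% | 80.2% |
| 51 | 80.3% | 80.0% |

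The loss is about 2 points by the approximation and about nil by exact calculation. Exact power is not smooth in n, which is why 49 and 51 look alike.

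**4. If missing counts as failure.** Two assumptions are needed that the protocol does not state: the loss d is the same in both arms, and 93.3% and 73.3% are rates among patients with observed outcomes. All 61 per group are then analysed, with rates p1(1 − d) and p2(1 − d). At d = 0.20 these are 0.933 × 0.8 = 0.746 and 0.733 × 0.8 = 0.586, a difference of 0.160. With unpooled variance the standard error is √[(0.1893 + 0.2425)/61] = 0.0841. Then 0.160/0.0841 = 1.902, and power is Φ(1.902 − 1.960) = 47.7%. The table gives the range from the normal approximation with pooled and with unpooled variance, next to the exact result.

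| Loss in each arm | Rates compared | Power, 61 per group | Exact chi-square |
|---|---|---|---|
| 5% | 88.6% vs 69.6% | 74–76% | 75% |
| 10% | 84.0% vs 66.0% | 63–65% | 65% |
| 15% | 79.3% vs 62.3% | 54–56% | 55% |
| 20% | 74.6% vs 58.6% | 46–48% | 46% |

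Moving to 64 per group does not repair this: at 20% loss power is still only about 48–50%. Under this rule and that loss, about 133 to 136 per group would be needed for 80%.

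**5. If multiple imputation is primary.** Missing outcomes are not set to failure, so the attenuation in step 4 does not apply.

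**The case against.** The strongest reply is that the certain error hardly matters. By exact calculation for the first-named test, 48 to 49 completers do about as well as 51. That stands: alone, the slip is a small shortfall and a text correction. The stated requirement is still wrong on its own figures, and no choice of test or rounding makes 61 × 0.8 reach 51.

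The second reply concerns the low power figures. A reader might infer that this trial simply has about 46% power. The documents do not support that, for three reasons. The failure rule is one of two, and {20c} plans multiple imputation. The 20% is a planning allowance; the protocol has retention measures and seeks a last assessment from dropouts, so actual loss may be lower. The planning rates come from a cited source that is not shown; if they already counted dropouts as failures, no attenuation would follow, although the 20% inflation would then not have been needed either. Likewise, a null result under the assumed effect becomes more likely than a positive one only from about 18% loss upward, not under the failure rule in general.

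A reader might also infer that 51 is itself too small, because other sample-size formulas give somewhat more. Exact power of 80.0% at 51 shows no defect there.

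**Conclusion.** The dropout allowance is wrong as written: on the protocol's own inputs, 51 after 20% loss corresponds to 64 per group (128), and 122 covers about 16% loss. This needs no assumption, and its effect on power is at most about 2 points.

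The two missing-data statements conflict, and the sample size is not tied to either. This is the more consequential part, but its size is conditional. If missing = failure is primary, the step 4 range applies, from 74–76% at 5% loss to 46–48% at 20%, given equal loss in the arms and planning rates based on observed outcomes. If multiple imputation is primary, it does not apply.

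**What to change.** In Sample size {14}, do one of the following:

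- give 64 per group (128 in total) as the number that keeps 51 after 20% loss; or
- keep 122 and state that it covers about 16% loss; or
- keep 122 and state that 20% loss leaves about 48 to 49 per group, with about 78% power by the formula used (79–80% by exact chi-square).

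Then reconcile Missing data with {20c}: name one rule for the primary analysis, make the other a sensitivity analysis if it is kept, and state power under the chosen rule. If missing = failure is chosen, show power over a range of loss rates and say whether the planning rates refer to patients with observed outcomes.

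The cost is a text amendment. No patients need be added if 122 is kept and its coverage restated; the first option adds six. The stated power may become less favourable, and if the failure rule is primary the sponsor should decide knowingly whether to accept it.

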### Recruitment {15}

We will use three major strategies to ensure adequate participant enrolment: (1) posting recruitment information in hospital areas, such as the outpatient hall; (2) posting recruitment information on WeChat, a popular communication platform; and (3) introduction of the trial to prospective patients by researchers during the treatment process; the researchers will ask the patients if they would like to participate.

## Assignment of interventions: allocation

### Sequence generation {16a}

The ResMan clinical trial public will be used as the central randomization tool to automatically generate random numbers. Participants will be required to register once they meet the inclusion criteria. Each participant will be provided an ID as a unique identification number and assigned to one of the two groups by logging on to the website of the randomization center.

### Concealment mechanism {16b}

The random coding table will be generated by the central random platform and sealed by the GCP specialist of Longhua Hospital and submitted to the project leader for preservation. The drugs will be packaged and confirmed as a blinded treatment by a GCP specialist at the Longhua hospital; the random codes will be mentioned on the drugs and the box label.

### Implementation {16c}

Random sequences will be generated by statisticians who will not participate in the implementation of the project. In addition, neither researchers nor patients will have access to the random sequences.

## Assignment of interventions: blinding

### Who will be blinded {17a}

All participants, subjects, and study monitors will be blinded until the trial is completed.

### Procedure for unblinding if needed {17b}

For emergency blinding, there will be an emergency envelope for every case, with information about the coding and groups. It is necessary to be aware of the drugs used by the patients in case of any serious event, and patients need to be treated. The project leader decides to initiate unblinding and open the corresponding emergency envelope. Once the emergency envelope is opened, the case is treated as a shedded case.

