### Criteria for discontinuing or modifying allocated interventions {11b}

The criteria for discontinuation are as follows: (1) if anaphylaxis or serious adverse events occur, the test should be terminated based on the physician’s decision; (2) during the study, two consecutive laboratory tests will be compared, and the results of laboratory tests should be factored in while judging treatment efficacy and safety; (3) patients with poor compliance in the study (compliance with experimental drug < 80%), those with automatic halfway dressing change, or those administered other Chinese and Western drugs prohibited by the party; (4) cases of blinding not maintained halfway through the study for various reasons; (5) regardless of reason, unwillingness or inability of the patient to continue with the clinical study, or request of withdrawal from the study to the competent physician; (6) loss of patients owing to non-acceptance of the drug or the test, even when the study case did not explicitly propose withdrawal from the study.

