### Outcomes {12}

#### Primary outcome

Cardiac function (from baseline to weeks 4, 12, and 24)
◦ Significant effects: cardiac function restored to level 1 or increased by level 2◦ Effective: heart function improved to level 1, but not to level 2◦ Invalid: no change in cardiac function◦ Deterioration: decrease in cardiac function by a single grade or more

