## Data collection and management

### Plans for assessment and collection of outcomes {18a}

In this 24-week trial, all participants will be treated with the Zhigancao Tang granules or placebo for 12 weeks, with follow-up continuing for another 12 weeks. Data will be recorded in the case report forms (CRFs) at each visit and entered in Microsoft Excel by two statisticians working independently.

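### Every emergency-unblinded patient is classed as 'shedded' (most naturally a dropout), which ties loss of follow-up to serious events. A minor point with a cheap fix

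*Protocol article*

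**What the plan says.** Procedure for unblinding if needed {17b} provides an envelope for each case and gives the reason for opening it: "It is necessary to be aware of the drugs used by the patients in case of any serious event, and patients need to be treated". It ends with an unconditional rule: "Once the emergency envelope is opened, the case is treated as a shedded case". The word 'shedded' is not defined anywhere in the article.

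Criteria for discontinuing or modifying allocated interventions {11b} lists, as criterion (4), "cases of blinding not maintained halfway through the study for various reasons". The two items after it concern withdrawal from the study and loss of patients.

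The schedule that an opened case would otherwise follow is clear. The primary outcome is "Cardiac function (from baseline to weeks 4, 12, and 24"), and Table 4 shows the same visits. Under Safety monitoring, "Adverse events and severe adverse events will be recorded at each visit". Section {18a} plans 12 weeks of treatment "with follow-up continuing for another 12 weeks".

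For gaps in the data, the Missing data paragraph counts a missing value as a failure, while {20c} specifies multiple imputation by chained equations. Section {20c} also plans an intention-to-treat analysis and advises researchers to try to obtain the last test from patients who drop out or are lost.

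**The concern.** Stopping study drug after a code break is defensible. Ending observation is a separate decision, and nothing about a broken code requires it: an unblinded patient can still be graded, tested and asked about adverse events.

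The {17b} rule applies to the case, not to the drug. If it is followed as most naturally read, patients who have had a serious event become dropouts by rule. Two things are at stake.

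- **Analysis.** The missing results are related to clinical events by construction. A failure score or an imputed value then replaces something that could have been observed. If code breaks are unequal between the groups, the comparison can shift in either direction.
- **Safety.** Section {22} covers the outcome of the event itself. Later adverse events are picked up at visits, which a dropout may no longer have, and these are the patients in whom later events matter most.

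**Working it through.** The plan gives no figure for code breaks, so there is none to reproduce. The check sets the texts together, counts visits, and adds one illustration on assumed counts.

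**1. Does 'shedded' mean dropout?** The rule in {17b} names the case. In {11b}, lost blinding stands beside study withdrawal (5) and loss of patients (6). Both fit dropout. The heading of {11b} concerns allocated interventions, so criterion (4) taken alone could mean stopping drug only. Dropout is therefore the natural reading but not a certain one.

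**2. Does other text keep the visits?** Section {18a} describes follow-up for all participants, and {18b} offers reminders and fares. These are general statements and do not override a specific rule for opened cases. Section {20c} is the only text on assessing dropouts. It is advisory, refers to a single last test, gives the intention-to-treat analysis as its purpose, and does not mention adverse events.

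**3. Visits at risk per opened case.** There are three post-baseline primary-outcome assessments: weeks 4, 12 and 24. Assessments still due = 3 minus those already done. The last test in {20c} could be one of the visits still due (subtract 1) or an exit test at dropout (subtract 0).

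| Envelope opened | Still due | No stated provision, last test is a due visit | No stated provision, last test is an exit test |
|---|---|---|---|
| Before week 4 | 3 | 3 − 1 = 2 | 3 |
| Weeks 4 to 12 | 2 | 2 − 1 = 1 | 2 |
| Weeks 12 to 24 | 1 | 1 − 1 = 0 | 1 |

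**4. Illustration of direction only.** Inputs from Sample size {14}: response rates 93.3% and 73.3%, 61 per group. Assumptions that are not in the documents: u opened cases in a group, all scored as failures, who would otherwise have responded at the planned rate. The expected rate in a group is then p × (61 − u)/61.

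| Opened cases, active / control | Active rate | Control rate | Difference |
|---|---|---|---|
| 0 / 0 | 93.3% | 73.3% | 20.0 points |
| 1 / 1 | 93.3 × 60/61 = 91.8% | 73.3 × 60/61 = 72.1% | 19.7 points |
| 3 / 3 | 93.3 × 58/61 = 88.7% | 73.3 × 58/61 = 69.7% | 19.0 points |
| 3 / 0 | 88.7% | 73.3% | 15.4 points |
| 0 / 3 | 93.3% | 69.7% | 23.6 points |

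Balanced openings barely move the difference; unbalanced ones can move it either way. The table overstates the shift to the extent that such patients would have failed anyway, that a last test is obtained, or that imputation is used instead of failure scoring. It shows the mechanism and does not estimate its size.

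**The case against.** The strongest reply is that the lost follow-up is inferred. The word 'shedded' looks like a translation, no sentence says that visits stop or data are discarded, and {18a} promises follow-up to all participants. A condensed article may leave the handling of a case after a code break to the full protocol. Scoring a patient with a serious event as a failure can also be a sensible conservative rule. Part of this stands: the reading is probable, not certain, and nothing shows that any envelope will be opened. But the criticism is of a rule that the article states without exception, not of a detail it omits, and failure scoring is no reason to forgo an observation that could be made. The choice between failure scoring and imputation affects all missing data and is a separate matter.

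A reader might also object to the sentence "The project leader decides to initiate unblinding and open the corresponding emergency envelope", and infer that one person could delay emergency care. The documents do not support this. They do not say that the project leader alone may act; that would be read from silence. They do not place the project leader off site, and no delay is shown. Nor is there a conflict with {11b}, where "if anaphylaxis or serious adverse events occur, the test should be terminated based on the physician’s decision": stopping the drug and breaking the code are different decisions, and the physician can do the first without the second. Centralised code-breaking is a reasonable way to protect the blind.

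**Conclusion.** The point holds as a minor one. As written, {17b} makes dropout the likely consequence of opening an envelope, so missing outcomes and missed adverse-event checks become tied to serious events. Between one and three primary-outcome assessments are still due per opened case. Advice to obtain one last test is the only stated mitigation.

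This rests on reading 'shedded' as dropped out. The effect on the trial result cannot be sized, because the documents give no rate of serious events or code breaks; it is probably small.

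A reader might go further and infer that opened cases are removed from the intention-to-treat analysis, or lose all their outcome data. The documents do not say so: {20c} plans that analysis, nothing takes an opened case out of it, and results collected before opening remain. What is at risk is later observed data, not membership of the analysis set.

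**What to change.** Replace the last sentence of {17b} with:

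> Study drug may be stopped after the envelope is opened; the patient keeps all remaining scheduled assessments through week 24, including adverse events, and stays in the intention-to-treat analysis with observed data, flagged as unblinded.

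State that criterion (4) in {11b} means stopping study drug only. It can then stay as it is.

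The cost is one sentence, a clarification and a short instruction to site staff. Recruitment is under way (Trial status), so the change goes through the amendment route in {25} and helps only openings still to come. The downside is that symptom reports and NYHA grading may be biased once the allocation is known; the Discussion already concedes that the primary outcome is subjective. The flag allows a check of whether the result depends on assessments made after unblinding.

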## Data collection and management

### Plans for assessment and collection of outcomes {18a}

In this 24-week trial, all participants will be treated with the Zhigancao Tang granules or placebo for 12 weeks, with follow-up continuing for another 12 weeks. Data will be recorded in the case report forms (CRFs) at each visit and entered in Microsoft Excel by two statisticians working independently.

### Plans to promote participant retention and complete follow-up {18b}

All researchers will be advised to treat the participants in a friendly and respectful way and be patient, answering all questions they may have while encouraging them to participate. If the patients find it difficult to reach the hospital, the round-trip fare will be reimbursed. The researchers will send reminders to the patients 2 to 3 days before each follow-up.

